## Abstract

**Background:**

Osteosarcopenia is geriatric syndrome defined as the concomitant occurrence of osteopenia/osteoporosis, and sarcopenia. Osteosarcopenia is a relatively new concept in geriatric medicine; however, it may increase the risk of fragility fractures, several morbidities and mortalities, and socioeconomic costs. Although resistance exercises and nutritional support—including protein, calcium, and vitamin D—are potential non-pharmacological management procedures, evidence is still lacking. The objective of this study was therefore to evaluate the effect of combined resistance exercise and nutritional support on the quality and quantity of bone and muscle in postmenopausal females with osteosarcopenia.

**Methods:**

This research proposal presents the protocol for a prospective, single-center, single-blinded, two-armed randomized controlled trial. Thirty-four participants with osteosarcopenia will be recruited and randomly divided into intervention and control groups; both groups will receive nutritional supplements (protein, 40 g; vitamin D, 1600 IU; calcium, 600 mg) daily. The intervention group will undergo 24 weeks of resistance exercise of increasing intensity, achieved through a three-phase step-up process. The primary outcomes will be the changes in skeletal muscle index and bone marrow density of the lumbar spine and femoral neck between the baseline and end of intervention (24 weeks). The secondary outcomes will be the body composition, whole body phase angle, physical function assessment, quality of life, psychological assessment, and bone turnover markers of participants, surveyed at multiple time points.

**Discussion:**

This randomized controlled trial may reveal the effect of resistance exercise and nutritional support on older postmenopausal women with osteosarcopenia. The results will provide evidence for developing proper non-pharmacological management guidelines for postmenopausal women.

**Trial registration:**

Clinical Research Information Service of Republic of Korea, KCT0008291, Registered on 16 March 2023, https://cris.nih.go.kr/cris/search/detailSearch.do/25262.

**Supplementary Information:**

The online version contains supplementary material available at 10.1186/s12877-024-04667-1.

## Background

Osteosarcopenia (OS) is a geriatric syndrome characterized by the loss of bone and muscle tissue [1]. Osteopenia or osteoporosis is defined as low bone quality and bone marrow density (BMD) measured by dual-energy X-ray absorptiometry (DXA) or quantitative computed tomography, with T-scores <-1.0 and -2.5, respectively [2]. Sarcopenia (SP) is defined as a skeletal muscle disease that presents with muscle mass loss, muscle weakness, and functional deficits [3]. With the aging population, the co-occurrence of both conditions (OS) is predicted to increase in the future; moreover, OS may increase patients’ risk of fragility fractures, several morbidities and mortalities, and socioeconomic costs [4–6].

In the past, these two conditions were treated as separate entities; however, muscle and bone are interconnected and share mechanical effects. Growth of the bone and muscle are also interactively coordinated by complex paracrine and endocrine signals [7]; therefore, the combination of these two geriatric conditions is not rare, and simultaneous treatment of both conditions is sometimes considered by geriatric physicians. In the last decade, several non-pharmacological treatment guidelines for patients with osteopenia or osteoporosis [8, 9] and SP [10–12] have been announced and utilized in clinical practice. However, neither pharmacological nor non-pharmacological treatment guidelines have been announced for OS. Understanding the pathophysiology of OS, and performing high quality associated interventions is mandatory prior to developing treatment guidelines.

Sedentary lifestyles and poor nutritional status—including protein, vitamin D, and calcium—are known to be key risk factors for OS [13]. Controlling these risk factors may be key to maintaining the quality of bone and muscle tissue in geriatric patients, and perhaps even reverse the pathologic conditions causing these catastrophic results. The FrOST Study (Franconian Osteopenia and Sarcopenia Trial) aimed to evaluate the effect of high-intensity resistance exercise (HI-RT) and protein supplementation on the quantity of bone and muscle in male patients with OS [14]. The trial reported the effects of HI-RT supplemented with protein (1.5 g/kg/day in the HI-RT group and 1.2 g/kg/day in the control group) and vitamin D (800 IU/day), demonstrating improvements in the Z-score for SP (standardized mean difference [SMD]: 1.40), BMD at the lumbar spine (SMD: 0.72) and total hip (SMD: 0.72), and functional parameters (hand grip strength and gait speed) after 18 months of the intervention [15]. Moreover, they demonstrated the safety of the interventions; most participants completed the intervention program, excluding one male who reported a short period of worsening arthritic pain. Due to the COVID-19 lockdown period, the same authors also evaluated the detraining effects of the same study population for approximately 6 months, finding that the intervention group lost approximately one-third of benefits gained from the intervention, and exhibited higher detraining effects than the control group [16]. These trials suggest that a combination of exercise and nutritional support could prevent a further decline in bone and muscle health, and even reverse the pathological conditions; however, continuous management may be the key to managing these patients.

Our study aimed to determine the effects of multidisciplinary interventions—including resistance exercise and nutritional support (protein, vitamin D, and calcium)—to halt or reverse the decremental aging process affecting the quantity and quality of bone and muscle in postmenopausal females with OS.

## Methods/design

### Overview of research design

This randomized controlled trial is a double-arm, assessor-blinded trial comparing the effects of resistance exercises combined with nutritional supplementation in postmenopausal females with OS aged ≥65 years in a tertiary urban medical hospital. We followed the SPIRIT guidelines [17], detailed in Supplemental Material 1. The CONSORT flow diagram of the study is provided in Fig. 1.

**Fig. 1 Fig1:**
[figure not shown]
Trial flow diagram

All patients will provide written informed consent, and the Chungnam National University Hospital's Institutional Review Board has approved the trial's ethical validity (CNUH 2022-12-026). The clinical trial is registered under the Clinical Research Information Service of Republic of Korea (KCT0008291).

### Participants

#### Eligibility criteria

Patients with sarcopenia and low bone mineral density (osteopenia or osteoporosis) are classified as osteosarcopenia (Fig. 2) [13]. Participants who fulfill the following criteria will be considered eligible for the study: 1) postmenopausal females aged between 65 and 90 years; 2) diagnosed with SP according to the Asian Working Group of Sarcopenia [11] (low appendicular skeletal muscle mass by dual energy X-ray absorptiometry [DXA; M<7.0 kg/m^2^, F<5.4 kg/m^2^] or bioelectrical impedance analysis (BIA; M<7.0 kg/m^2^, F<5.7 kg/m^2^]; low muscle strength, defined as low grip strength [<28 kg for males, <18 kg for females]; or low physical performance, defined as <1.0 m/s in the 6 meter-walking test, ≤9 points in the Short Physical Performance Battery [SPPB], or ≥12 seconds in the Five Times Sit-to-Stand test); and 3) low bone mineral density diagnosed with osteopenia (T-score ≤-1.0 on DXA) or osteoporosis (T-score ≤-2.5 on DXA) [18].

**Fig. 2 Fig2:**
[figure not shown]
Diagnosis of osteosarcopenia. Patients with sarcopenia or low bone mineral density (osteopenia or osteoporosis) categorized as having osteosarcopenia. The authors utilized diagnostic criteria for sarcopenia as outlined by the Asian Working Group of Sarcopenia.; low appendicular skeletal muscle mass by dual energy X-ray absorptiometry [DXA; M<7.0 kg/m2, F<5.4 kg/m2] or bioelectrical impedance analysis (BIA; M<7.0 kg/m2, F<5.7 kg/m2]; low muscle strength, defined as low grip strength [<28 kg for males, <18 kg for females]; or low physical performance, defined as <1.0 m/s in the 6 meter-walking test, ≤9 points in the Short Physical Performance Battery, or ≥12 seconds in the Five Times Sit-to-Stand test. Low bone mineral density is classified as osteopenia (between −1 SD and −2.5 SD T-score) and osteoporosis (< −2.5 SD T-score) according to the World Health Organization criteria

#### Exclusion criteria

The exclusion criteria will be as follows: 1) secondary osteoporosis; 2) regularly taking medications that can affect the bone or muscle more than a month before the study (e.g., anticonvulsants, steroids); 3) a diagnosis of diabetes mellitus, thyroid disease, parathyroid disease, or Paget’s disease of bone; 4) active malignancy requiring treatment; 5) having implants, hardware, devices, or foreign material in the measurement area; 6) chronic kidney disease more severe than stage 3 (GFR<60 ml/min); 7) alcohol addiction; 8) a history of previous fragile fractures (radius, hip, or spine); 9) inability to understand or to participate in the study protocol; and 10) refusal to participate. In the case of patients affected by secondary osteoporosis, diabetes mellitus, thyroid disease, parathyroid disease, Paget’s disease of bone, or active malignancy, the authors exclude these individuals from the study due to the potential impact of these disorders on study results. The presence of implants, hardware, devices, or foreign material in the measurement area is considered inappropriate in this study due to the remodeling of adjacent tissues around the material in measuring the bone and body composition by DXA scan [19]. Chronic kidney disease more severe than stage 3 is regarded as a contraindication for a high-protein diet [20]. Furthermore, patients with alcohol addiction or a history of previous fragile fractures are also excluded from the study protocol due to the risk of falls or further fractures.

#### Exit criteria

The exit criteria will be as follows: 1) participants’ request, 2) serious side effects preventing further participation, and 3) not completing the entire study protocol.

### Randomization, allocation, and blinding

The study coordinator initially evaluated volunteered community-dwelling post-menopausal old female in Daejeon, Korea. After checking the inclusion criteria, eligible participants will be asked for consent to enroll in the study. After obtaining informed consent, all participants will be randomly assigned to two groups (1:1 allocation): the resistance exercise group and control group. Block randomization of four blocks will be used to balance allocation. After randomization, the study coordinator will handle participant allocation findings in a private manner. A single, trained physical therapist who is blinded to the participant groups will conduct each assessment for this study. Due to the nature of the study, participants allocated to the resistance exercise group will visit our gym twice per week, and will not be blinded. To ensure confidentiality and minimize potential bias, all participants will be instructed to avoid communication with any other researchers or physiotherapists regarding their allocated group.

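### The study coordinator both evaluates volunteers and handles the allocation results under blocked randomization, so later assignments may be partly predictable at screening

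*Protocol article*

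**What the plan says.** All of the relevant text is in the Protocol article, section Randomization, allocation, and blinding.

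- Evaluation of volunteers: "The study coordinator initially evaluated volunteered community-dwelling post-menopausal old female in Daejeon, Korea".
- Consent, with no role named: "After checking the inclusion criteria, eligible participants will be asked for consent to enroll in the study".
- Block structure, for a 1:1 allocation: "Block randomization of four blocks will be used to balance allocation".
- Allocation results: "After randomization, the study coordinator will handle participant allocation findings in a private manner".
- Blinding of outcome assessment: "A single, trained physical therapist who is blinded to the participant groups will conduct each assessment for this study".
- Participants in the exercise arm: "participants allocated to the resistance exercise group will visit our gym twice per week, and will not be blinded".

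Participants are also told not to discuss their group with other researchers or physiotherapists. The Discussion lists volunteer sampling and small size as limitations and describes the randomization as proper. It does not mention predictability of assignment.

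**The concern.** One role appears at both ends of the process: it evaluates volunteers before entry and handles the assignments afterwards. Blocking makes each assignment depend on the earlier ones in the same block. Someone who knows those and the block size can therefore sometimes know, and often guess, which arm comes next while the next volunteer is being evaluated.

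The safeguards in the text (private handling, the instruction not to communicate, the blinded therapist) protect outcome assessment. None of them keeps past assignments from the person who screens the next woman. If that knowledge influenced who entered or when, the arms could differ in fitness or motivation from the start, and a blinded DXA measurement would faithfully record the difference. The primary comparison described under Statistical analysis is a t-test or Mann-Whitney test on changes, which would not absorb such an imbalance.

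**Working it through.** **Inputs from the article.** 34 women (Abstract; 17 per group in Sample size calculation, 2 × 17 = 34), 1:1 allocation, and the four-blocks phrase. The article gives no figure on predictability, so there is none to reproduce.

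**Assumptions.** Entry is sequential. The coordinator knows the block size and all earlier assignments in the current block. The phrase is read in two ways: blocks of size four, or four blocks in total. For the second reading the sizes are assumed to be 8, 8, 8 and 10, which sum to 34.

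**Formulas**, for a block of size b with all orders equally likely:

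- Expected number of certain assignments: b / (b/2 + 1).
- Expected correct guesses when always naming the arm with more places left (ties count one half): b/2 + 2^b / (2 × C(b, b/2)) − 1/2.

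**Check for b = 4 by listing the six orders.** AABB and BBAA each make the last two places certain. The other four orders make only the last place certain. Total (2 × 2 + 4 × 1) / 6 = 8/6 = 1.33, which matches 4/3. Correct guesses by place: 1/2 + 2/3 + 2/3 + 1 = 2.83, which matches 2 + 16/12 − 1/2.

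| Block size | Certain per block | Correct guesses per block |
|---|---|---|
| 4 | 1.33 | 2.83 |
| 8 | 8/5 = 1.60 | 4 + 256/140 − 0.5 = 5.33 |
| 10 | 10/6 = 1.67 | 5 + 1024/504 − 0.5 = 6.53 |

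**Blocks of four, 34 women** (eight full blocks and two places of a ninth):

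- Certain: 8 × 1.333 = 10.7; 10.7/34 = 31%.
- Correct guesses: 8 × 2.833 + 1/2 + 2/3 = 23.8; 23.8/34 = 70%.

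**Four blocks in total (8, 8, 8, 10):**

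- Certain: 3 × 1.60 + 1.67 = 6.5; 6.5/34 = 19%.
- Correct guesses: 3 × 5.329 + 6.532 = 22.5; 22.5/34 = 66%.

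Chance alone gives 50% correct guesses.

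**Would varying the block size be enough?** In a simulation of 3,000 trials of 34 women, block sizes were drawn at random from 4 and 6. The guesser knew the two possible sizes and saw every past assignment. Certain assignments fell to about 6%, but best-guess success stayed near 69%. Varied blocks remove most of the certainty and little of the guessing.

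**Illustration of the effect on a result.** Suppose every woman entered when an arm is predicted differs by h SD in expected change, upwards when exercise is predicted and downwards when control is predicted. The article gives no value for h; a range of 0.1 to 0.5 is assumed. The expected false difference is (correct − wrong guesses) × h / (women per arm).

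- Complete blocks of four: (2.833 − 1.167) / 2 = 0.83h, or 0.08 to 0.42 SD.
- Four blocks in total: (22.52 − 11.48) / 17 = 0.65h, or 0.06 to 0.32 SD.

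For comparison, the design effect for SMI is d = 1.53 (Sample size calculation). The Background cites 0.72 for BMD from an earlier 18-month trial. The illustration assumes full exploitation and is not a prediction.

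**The case against.** The strongest reply is that the article describes less than full foreknowledge. It says that the coordinator evaluates volunteers initially and handles results after randomization. It does not say that the coordinator makes the final eligibility decision, sets the time of entry, generates the list or knows the block size. Evaluating all volunteers first and randomizing them afterwards would also fit the wording. A recruitment period from March to November 2023 (Trial status) points to sequential entry but does not settle it. This stands, and it is why the figures are conditional upper bounds.

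Room for discretion is also limited. Entry rests largely on measured cut-offs for muscle mass, grip, physical performance and T-score (Eligibility criteria), and on kidney function and listed diagnoses (Exclusion criteria). What remains is mainly exclusion 9, on ability to understand or take part, and the timing of entry. This stands too, and narrows the risk without closing it.

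A third reply is that concealment mechanics belong in the full protocol. That is right: the absence of a named list holder or release method from an article is no finding. The point rests on the stated double role, and having someone else generate the list would not by itself resolve it.

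A reader might infer more than the text supports:

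- that the coordinator also takes consent: no role is named;
- that the trial is simply open-label: exercise participants are unblinded, but the assessor is blinded;
- that 34 not being a multiple of four is a fault: an incomplete last block is routine, the target is at least 17 per group, and divisibility has no bearing on selection bias.

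**Conclusion.** The point holds as a stated arrangement that is open to selection bias. One role evaluates volunteers and handles allocation results under blocked 1:1 randomization, and none of the stated safeguards separates the two tasks. If entry is sequential and the block size is known, 31% of assignments are certain and 70% can be guessed with blocks of four; 19% and 66% with four blocks in total. The second pair depends on the assumed sizes 8, 8, 8 and 10.

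It would be tempting to conclude that women were steered into the gym arm, or that allocation was not concealed. The article supports neither: the risk is potential, and no imbalance or misuse is shown. The sample size calculation is not affected. The arrangement should be corrected or, if it is too late for that, disclosed.

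**What to change.** **If women remain to be allocated.** Separate the roles. An existing team member who does not screen, consent, train or assess holds the list and the running allocations, and releases each assignment only after eligibility and baseline measures are recorded. Undisclosed, varied block sizes can be added as a supplement; alone they are not sufficient. Replace the four-blocks phrase with the actual block size or sizes in the report or study record, without disclosing them to recruiting staff while allocation continues.

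**If recruitment is complete**, as the planned November 2023 end suggests. Report the block size, who held the list and whether the screening coordinator could see earlier allocations. Acknowledge possible selection bias as a limitation. Baseline SMI and BMD can be compared by how predictable the assignment was, as a descriptive check only: with blocks of four it sets about 11 women against about 23, so its power is low and a null result would not be reassuring.

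**Cost.** A small change in team duties and a few sentences of text, and possibly a difference of one or two women between arms. No extra participants or procedures are needed. If the full protocol already separates the roles, one corrected sentence closes the point.

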In phase 2 (9–16 weeks after allocation), participants will be asked to increase the weight of the exercise until 7–10 reps are possible; the nRM will be applied to their exercise (maximum effort minus 1). Movement velocities will also be adjusted to 4 seconds of concentric, 1 second of isometric, and 4 seconds of eccentric phase per repetition. Otherwise, the same principles will be applied as in phase 1.

In phase 3, participants will be asked to apply the concept of the RM—defined as a “set endpoint when trainees complete the final repetition possible whereby if the next repetition was attempted, they would definitely achieve momentary failure” [21]—to each exercise. They will perform the number of repetitions judged to be possible in range of 7–10 reps. When the exercise intensity is increased to a high intensity, periodization is applied, including 3 weeks of high-intensity exercise (RM) and 1 week of moderate-intensity exercise (nRM, same as in phase 1) during the intervention period. In total, 60 minutes of exercise (10 minutes warm-up, 40 minutes main exercise, 10 minutes cool-down exercise) will be performed per session. Brief descriptions of the exercise protocols are depicted in Fig. 3.

**Fig. 3 Fig3:**
[figure not shown]
Protocol for exercise intervention, Reps, Repetitions; nRM, Nonrepetition Maximum; RM, Repetition Maximum

Control groups will be provided with exercise brochures and encouraged to perform home exercise daily. The exercise brochures (Supplemental Material 2) will include stretching, balance training, back extensor strengthening, and other strengthening exercises. Performing home exercise at least twice per day will be instructed and encouraged.

### Nutritional supplementation

Basal nutritional surveys using 24-hour recall methods will be performed in both groups (exercise and control groups) by a trained dietician. Total calorie and protein intake will be assessed, and the Mini Nutritional Assessment-Short Form at T0 (0 weeks)—with the score ranging from 0–14 points—will be evaluated to assess the nutritional status of participants [22].

Protein supplementation during resistance exercises is known as significantly increasing the muscle size and strength in healthy adults [23]. In our study, two packs of protein complex powder (Selex core-protein; protein: 20 g [50% casein + 40% whey + 10% soy, total leucine: 3000 mg], vitamin D: 800 IU [20 µg], calcium: 300 mg, fat: 1.1 g, carbohydrate: 2.5 g; Maeil Dairies Co., Ltd., Seoul, South Korea) will be provided in daily basis; therefore, a total of 40 g of protein, 1600 IU of vitamin D, and 600 mg of calcium will be provided for the 24-week program in all participants, regardless of allocated group.

### Outcome measurement and participants’ timeline

The primary outcomes of this study are changes in the skeletal muscle index (SMI) and BMD of the lumbar spine and total hip between the baseline and end of the intervention. The SMI is an indicator of skeletal muscle mass, which is calculated as the appendicular skeletal muscle mass divided by height squared (kg/m^2^). The secondary outcomes are quality of life measurement, functional assessment, bone turnover marker (C-telopeptide [type 1 collagen], CTX), BIA assessment (including body composition and whole-body phase angle), and muscle quality index (MQI). Participants will be screened for adverse events from study inclusion, to the end of the intervention. The schedule of the trial is illustrated in Fig. 4. After obtaining informed consent, basal measurements including demographic details (sex, age, height, weight, alcohol consumption, smoking history, and other medical history) will be surveyed by the research delegate. Weight (kg) divided by the height squared (cm^2^) will be used to compute the body mass index (BMI). Blood samples in fasting status will be collected from the antecubital veins of participants, and analyzed within 24 h of sampling. Albumin, pre-albumin, calcium, parathyroid hormone, serum vitamin D, creatinine levels will be evaluated at T0 (0 weeks).

